#### Characterize IETP Participants

We will begin characterization with the Tampa site (n=approximately 350) and Richmond site (n=approximately 150), followed by other sites. We will use VA and DoD health system data to characterize preadmission military and sociodemographic characteristics, TBI-related diagnoses (eg, PTSD, pain, and sleep), and medication use (eg, opioids, antidepressants, and sedative hypnotics). We will add data from TBI history and symptom inventories administered at IETP admission to develop mild TBI phenotypes [36,41,42]. This allows the characterization of participants in the IETP and the identification of groups that are likely to have similar courses of care.

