**Knowledge to implementation (implementation stage)**			
	Aim 1: characterize the degree of implementation	IETP innovations have occurred asynchronously with variation of implementation	Qualitative data collection with a purposive sample of clinicians at each site to understand the degree of implementation, inform selection, and tailor implementation to each site
	Aim 3: disseminate and promote IETP implementation	Continued funding for TBI rehabilitation services in a competitive fiscal environment across the VA organizational hierarchy	Use participatory approach to (1) promote a bottom-up pull for “IETP evidence-based” practices, (2) disseminate implementation content, and (3) gather feedback for each site. Leverage existing reporting structures to summarize findings for reports to Congress including VA and DoD administrators, and clinicians for uptake and sustainment

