#### Measures and Data Collection Procedures

Data from each IETP participant will be obtained from site leads beginning with Tampa (2015 to present; n=approximately 350). We will obtain identifiers that allow linkage to VA and DoD health system data and create a study crosswalk database behind the VA firewall that includes the encrypted identifier, a study ID, and contact information for interview and survey administration. We will obtain intake and discharge measures from each IETP site. We will assess IETP fidelity based on the IETP characterization table (Multimedia Appendix 1) using a checklist (Multimedia Appendix 2) and chart abstraction focusing on the admission note, admission IETP care plan, discharge TBI care plan, and discharge summary, which are highly accurate in describing the reasons for seeking treatment, baseline status, the type of treatment recommended, the type of treatment received, and outcomes on discharge (Multimedia Appendix 12).

We will also link these IETP data to VA and DoD health system data, as we have done previously [36], to obtain information on physical and mental health, medications, and military demographic data before and after IETP. As approximately 90% (225/250) of participants in the IETP are active duty at the time of treatment with the goal of returning to full duty and operational partner priority outcomes include return to duty or employment, the use of VHA data (eg, Patient Health Questionnaire-9 [PHQ-9] and PTSD checklist-5) is not a feasible approach to long-term outcomes. Therefore, we will conduct a survey using a VA-approved web-based survey software for participants of IETP (2015-2022; approximately 500) using a Modified Dillman Method, which we used in prior VA studies (Multimedia Appendix 13) [37-40]. We will begin a survey of earlier IETP graduates in the first year of the study and send surveys to new graduates 6-9 months post study completion. The final outcome measures included in the survey will be developed in collaboration with stakeholders. The current list of stakeholder-identified measures that are evaluated at intake and discharge include the PHQ-9, PTSD checklist-5, MPAI, and the Neurobehavioral Symptom Inventory.

We will also use VA and DoD health system data to describe health system outcomes such as use, new diagnoses, and adverse outcomes, which will, together with data baseline, discharge, fidelity, and discharge outcomes, be used to develop trajectories of recovery.

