#### Identify Treatment Received During IETP

Consistent with prior studies [50-52], we will create an abstraction tool in collaboration with IETP clinicians and aim 1 data. Using the crosswalk database, we will conduct chart abstraction for IETP focusing on the initial assessment, TBI care plan, processes and amount of care received, discharge assessment, and TBI care plan. After finalizing the procedures and appropriate training, team members will independently review 10 charts and then meet to identify inconsistencies, errors, or disagreements and resolve any by consensus. This will continue until there is 90% agreement on all items abstracted, to ensure abstraction fidelity. The areas of uncertainty will be discussed with IETP clinicians. These data will be merged with IETP data, VA and DoD analytic file data, and survey data for the outcome analyses.

We will identify what happens during the IETP stay using descriptive statistics for the overall cohort, stratified by phenotypes from the measures listed in the *Measures and Data Collection Procedures* section. We expect that different types of care will be provided to individuals with different prior comorbidities and clinical presentations. We will apply Pearson chi-square test to assess the association between recommendations for admission TBI care plan and TBI phenotype.

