#### Identify Components of IETP Associated With Sustainment and Improvement Trajectories

Outcomes currently identified by operational and clinical stakeholders that are collected at all sites (Tables 3 and 4) will be included in the survey to develop longitudinal outcome trajectories. On the basis of stakeholder feedback, we will also measure and describe community reintegration, employment, retention in the military where relevant, compliance to discharge from the TBI care plan, reasons for difficulty in care plan compliance, and unmet rehabilitation needs. Per operational partners’ request, we will also use VHA and DoD data to identify use relevant to discharge (eg, TBI care plan within primary, mental health, specialty care, or emergency care).

We will use Bayesian network analysis to generate a directed acyclic graph, which probabilistically describes the trajectory of symptoms, care, and outcomes for IETP participants. This network will enable us to explore the contribution of the baseline phenotype to the decision to use a particular treatment course and the contribution of those treatments to the participants’ resulting outcome measures [53]. Using a hill-climbing algorithm scored with the Bayesian information criterion, we will establish directional connections between nodes, called edges, and evaluate the robustness of the edges using bootstrapped samples of the data. We will a priori exclude any implausible directed edges (eg, IETP care cannot lead to precare symptoms). The resulting directed network will have edges between the levels: (1) phenotypes, (2) treatment, and (3) outcomes, while disallowing connections that go from levels 2 to 1 or 3 to 2 or 1. We can allow edges between nodes within the treatment level of the network to better understand the interactions between treatments and to assess how the treatments individually and in combination probabilistically affect patient outcomes. By fitting this model, we can isolate the most probable trajectories between TBI phenotypes and treatments and then determine which treatments have a higher probability of positive long-term outcomes. To gain an understanding of the treatment courses on outcomes, we will present a graphical display of the nodes and edges, the conditional probabilities calculated between nodes that estimate the probability of long-term outcomes given the participants’ IETP components and comorbidity phenotypes, and the robustness measures from bootstrapping.

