#### Power and Missing Data

The analyses in this aim take an exploratory approach to establishing phenotypes with latent variable mixture models and isolating common trajectories based on Bayesian networks. As such, we do not have a targeted hypothesis with which to power this analysis for minimum detectable effect sizes but rather a model selection approach using the Bayesian information criterion. With 500 participants, we expect that our sample size will be well above the number of nodes in the Bayesian network, which will allow for an accurate estimation of the conditional probabilities in the network [54,55].

We will assess the risk of bias owing to missing data by looking at patterns of missing measurements at each phase of the patients’ trajectories, although we expect most missingness to be postdischarge. Reasons for missing measurements will be tabulated with a focus on differentiating missed measurements for logistical reasons from dropouts or intermittent missingness potentially related to the condition of the patient. If >10% (25/250) of the patients have missing outcome measurements for any of the follow-up measures or if the comparisons of baseline characteristics between patients with missing and nonmissing measurements indicate considerable imbalances, rather than only looking at complete cases, we will apply the structural expectation-maximization algorithm, an imputation method that directly processes data with missing values while fitting the Bayesian network [56]. This method incorporates baseline and follow-up factors beyond the variable being analyzed to account for the dependence of missing data on other factors. TBI history is a primary piece of data required for admission to the program. It is unlikely that any data will be missing for TBI history. However, if >20% (>50/250) of the sample has missing data related to TBI history, the study should be stopped.

### Aim 3

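### As described, the Aim 2 network and chi-square test are not adjusted for site, and the stated 500 already equals the Tampa and Richmond counts although five sites are to contribute

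*Protocol article*

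**What the plan says.** **Analyses.** In the protocol article, the Aim 2 section on identifying components associated with trajectories describes a Bayesian network built by hill-climbing on the Bayesian information criterion (BIC). It will have "edges between the levels: (1) phenotypes, (2) treatment, and (3) outcomes", with backward edges between levels barred. In the section Identify Treatment Received During IETP, care during the stay is described overall and by phenotype, and "We will apply Pearson chi-square test to assess the association between recommendations for admission TBI care plan and TBI phenotype". Site is not named as a node, stratum or covariate in either place. The one stated comparison between sites is the qualitative matrix analysis of Aim 1.

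**Variation between sites.** Table 1 (implementation stage) records that "IETP innovations have occurred asynchronously with variation of implementation", and its preimplementation rows distinguish fully from partially implemented sites.

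**Numbers.** Characterize IETP Participants states: "We will begin characterization with the Tampa site (n=approximately 350) and Richmond site (n=approximately 150), followed by other sites". The survey is for "participants of IETP (2015-2022; approximately 500". Power and Missing Data justifies the network thus: "With 500 participants, we expect that our sample size will be well above the number of nodes in the Bayesian network". The Aim 2 measures section also plans to take intake and discharge measures from every site.

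**Use.** The Conclusions make the component results the basis for later implementation of effective components and withdrawal of ineffective ones.

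**The concern.** If sites differ both in how often they deliver a component and in how their patients fare for other reasons, site is a common cause of treatment and outcome. A network without site then has no way to separate the component from the place that delivers it. The bias can go either way. If the site that uses a component more has better outcomes, a component with no effect looks helpful. If it has worse outcomes, a helpful component can look ineffective and become a candidate for withdrawal.

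The chi-square test has the same structure. If sites differ in phenotype mix and in local care-planning habit, the pooled table can show an association that is absent within sites, or mask one that is present.

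The sample figure matters because the network is justified by it, and because a reader cannot tell from it how much evidence each of the five sites will supply.

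**Working it through.** **1. The plan's own figure.** Tampa about 350 and Richmond about 150 (Characterize IETP Participants): 350 + 150 = 500. This equals the survey population and the network sample. Tampa's share is 350/500 = 70%.

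The other three sites have no stated number. If they add patients beyond 500 (assumed *m* each), Tampa and Richmond together supply 500/(500 + 3*m*):

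- *m* = 10: 500/530 = 94%
- *m* = 25: 500/575 = 87%
- *m* = 50: 500/650 = 77%
- *m* = 100: 500/800 = 63%

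Patients from all five sites are clearly intended. Table 2 plans 12 patient telephone interviews per site (60 in all), and their contact details are to come from the Aim 2 data.

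**2. Expected false difference from pooling.** Take two sites with weights 0.7 and 0.3 and a component with no effect within either site. Let *d*c be the gap between sites in component use and *d*o the gap in good outcome, each centred on 50% (assumed). Pooled use is *p* = 0.5 + 0.2 × *d*c, and the pooled difference in outcome between those with and without the component is

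0.7 × 0.3 × *d*c × *d*o / [*p*(1 − *p*)].

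- Gaps 10 and 10 points: 0.21 × 0.1 × 0.1 / (0.52 × 0.48) = 0.8 points
- Gaps 30 and 15 points: 0.21 × 0.3 × 0.15 / (0.56 × 0.44) = 3.8 points
- Gaps 50 and 20 points: 0.21 × 0.5 × 0.2 / (0.60 × 0.40) = 8.8 points

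**3. How often that becomes a finding.** Simulation with 350 and 150 patients, complete outcomes, a null component within each site, and 2,000 runs per setting. The test level of 0.05 is assumed. A pooled edge is counted when the likelihood-ratio statistic G² exceeds ln *N*. Given site, G² summed over the two sites must exceed 2 ln *N*.

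| Gap in use / outcome (points, assumed) | Pooled Pearson rejects | Site-stratified Cochran-Mantel-Haenszel rejects | False BIC edge, pooled | False BIC edge, given site |
|---|---|---|---|---|
| 10 / 10 | 6.0% | 5.5% | 1.6% | 0.2% |
| 30 / 15 | 14.1% | 5.0% | 5.9% | 0.3% |
| 50 / 20 | 47.7% | 4.6% | 26.4% | 0.0% |

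Simulation error at a 5% rate is √(0.05 × 0.95/2000) = 0.5 points, so the two tests in the first row cannot be told apart. With no gap in use, the pooled edge rate was 1.4% to 1.6%, against 0.2% to 0.4% given site. That part of the difference between the two edge columns comes from the heavier penalty, not from confounding. The same calculation serves for two phenotype groups against a yes/no recommendation, with the gaps read as differences between sites in phenotype prevalence and in recommendation rate.

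**4. How much of component use lies between sites.** The between-site share of variance is 0.21 × *d*c² / [*p*(1 − *p*)]: 0.8% for a 10-point gap, 7.7% for 30, 22% for 50 and 60% for 80.

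**The case against.** **The levels are not a node list.** They restrict edge direction, and nothing bars site from being a baseline node. A fuller analysis plan, not shown, may include it. That is fair as far as it goes. But the article sets out the levels, the barred edges, the stratifier and the test in some detail, and site appears in none of them. Nor is it mentioned under Potential Limitations.

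**Site differences are partly handled.** Phenotype carries part of the case mix, fidelity is assessed by checklist and chart abstraction, and Aim 1 compares sites qualitatively. This reduces the problem but does not remove differences in referral, era, local practice or survey response.

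**BIC is conservative.** Adding an edge at *N* = 500 needs G² above ln 500 = 6.2, a null rate of about 1.3%. With assumed delivery of 90% v 50% and good outcome in 60% v 45%, the pooled difference is 57.1% − 49.8% = 7.3 points, yet the expected table gives G² = 1.9 and the false edge entered in only 13% of runs. This stands: the risk is a raised false-edge rate, not a certain false result.

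**The chi-square is descriptive and the aim exploratory.** A marginal association is a legitimate description, so the pooled test may stay beside a stratified one. Exploratory status does not excuse leaving out a known variable when the results are to inform withdrawal of care.

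**Stronger readings a reader might infer.** One is that three sites are excluded. The counts are approximate, 500 is never called a cap, and the text says other sites follow. Another is that component receipt depends strongly on site, so that five-site conclusions are largely a contrast of Tampa with Richmond. The protocol gives no component rates by site, and an unadjusted estimate mixes within-site and between-site information: even a 50-point gap puts only 22% of the variance in use between sites. A third is that the bootstrap must overstate edge stability and should be stratified by site. Nothing in the document establishes this, and fixing site counts in each resample would not cure it.

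**Conclusion.** The point holds in limited form. As the article describes them, the component-outcome network and the phenotype-by-recommendation test are unadjusted for site, while the same document says implementation varies by site. Site is therefore a plausible confounder of results meant to guide implementation and withdrawal. How much it matters cannot be settled from the protocol. Under assumed site gaps, the effect runs from almost none (10 and 10 points) to a pooled test that rejects a true null about half the time and false edges in about a quarter of runs (50 and 20 points). These figures assume two sites of 350 and 150, binary variables and complete outcomes.

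Separately, and without any assumption, the Tampa and Richmond counts add up to the 500 used for the survey and the network, while three further sites are to contribute with no stated number. This is an unreconciled planning figure. The change is worth making before the network is fitted.

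**What to change.** 1. Add site as a root node (small sites grouped) that may point to phenotype, treatment and outcome.
2. Use a site-stratified test of the Cochran-Mantel-Haenszel type for recommendation by phenotype, in place of or beside the pooled chi-square.
3. Repeat the network leaving out one site at a time, and report which component-outcome edges persist. This is needed even with a site node, because the score may drop a weak site edge.
4. State the expected number of patients per site, and reconcile the 500 with the five-site intent.
5. Report any component used at only one site as not separable from site.

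**Cost.** Site should already be known for each record, since data come from the site leads, so this is a change of wording and code. The price is somewhat wider uncertainty. Conditioning on site also raises the BIC penalty, so weak true edges will be harder to retain. Leave-one-site-out results without Tampa will be imprecise, and some components will have no separable estimate.

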#### Data Analysis

After calculating descriptive statistics (proportions and quantiles for discrete variables and means and SDs for continuous variables) of VHA and DoD intake measures before IETP admission, we will fit a latent variable mixture model, a multivariate statistical technique used to classify individuals into interpretable categories based on a set of measurements (described in the *Measures and Data Collection Procedures* section) [36,42-49]. Similar to cluster analyses, the latent variable mixture model is an exploratory technique to identify underlying constructs associated with multiple variables, in our case, the underlying comorbidity phenotypes. On the basis of prior work, we expect 2 to 3 groups each with n=approximately 100-200 participants [36]. Health system data identifying the treatment provided are not likely to have missing data owing to the professional responsibility to document. Each visit requires a primary diagnosis for care, which will lead to data available at each visit; therefore, we expect little to no missing data.

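### Near-complete linked data are inferred from every visit carrying a diagnosis; that holds per visit, not per person, so people without visits or outside VA and DoD care may be misread as condition-free or event-free

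*Protocol article*

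**What the plan says.** The completeness statement stands in Aim 2, Data Analysis, directly after the latent variable mixture model that forms the comorbidity phenotypes. It has two premises. The first is documentation by clinicians: "Health system data identifying the treatment provided are not likely to have missing data owing to the professional responsibility to document". The second is that every visit has a primary diagnosis, "which will lead to data available at each visit; therefore, we expect little to no missing data".

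The linked data are used at both ends of the analysis:

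- **Before admission** (Characterize IETP Participants): "We will use VA and DoD health system data to characterize preadmission military and sociodemographic characteristics, TBI-related diagnoses", together with medication use.
- **After discharge** (Aim 2, Measures and Data Collection Procedures): "We will also use VA and DoD health system data to describe health system outcomes such as use, new diagnoses, and adverse outcomes". These feed the recovery trajectories. Table 4 lists diagnoses, health care use, and medications and procedures for the periods before, during and after IETP.

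On coverage, the same Measures section reports that "approximately 90% (225/250) of participants in the IETP are active duty at the time of treatment" and concludes that using VHA data, with the PHQ-9 and PTSD checklist-5 as examples, "is not a feasible approach to long-term outcomes". A survey is added for that reason.

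Power and Missing Data plans for "looking at patterns of missing measurements at each phase of the patients’ trajectories, although we expect most missingness to be postdischarge". It applies structural expectation-maximization (EM) if more than 10% of patients lack outcome measurements on any follow-up measure, or if baseline characteristics differ considerably between patients with and without measurements.

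**The concern.** The premise concerns visits and the conclusion concerns the data set. Completeness per visit says nothing about a person who made no visit in the period, or whose visits took place outside the two linked systems. In visit-based records such a person has no blank field. Unless an observable period is defined, no visit, no condition and no coverage all look the same.

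Phenotypes and outcomes are the first and third levels of the Bayesian network, and linked data enter both. The Conclusions say that the results will be the foundation for implementing effective components and deimplementing ineffective ones. If coverage differs between phenotypes, sites or treatment courses, part of an apparent link between a component and an outcome could reflect who remained visible.

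**Working it through.** The article gives no coverage figure, so there is no stated number to reproduce. The check has two parts.

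**1. The passages side by side**

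- *Does the premise reach the person level?* No. Both reasons, the duty to document and a diagnosis at each visit, apply only once a visit inside the linked systems has taken place.
- *Does the article foresee people leaving coverage?* Indirectly. About 90% (225/250) are on active duty at treatment, and retention in the military is among the outcomes to be measured. The survey cohort runs from 2015 to 2022, which leaves time for separation.
- *Does the survey replace the linked outcomes?* No. It carries the four scales in Table 3 and items such as employment and unmet needs. The Measures section then adds use, new diagnoses and adverse outcomes from linked records.
- *Would the missing-data rule catch the gap?* Only if the value is recorded as missing. Both triggers, more than 10% missing and baseline imbalance, compare patients with and without a measurement. A person without a record who is entered as none counts as measured.

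**2. Illustration of size, if no record were read as none**

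All inputs here are assumptions:

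- share leaving service: 20% to 40%
- share of leavers not using VA care: 20% to 40%
- adverse-outcome rate in the observed: 15%
- risk in the unobserved relative to the observed, RR: 1.5 to 3

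Formulas:

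- Unobserved share u = (share leaving) × (share of leavers not using VA care), so 0.20 × 0.20 = 0.04 up to 0.40 × 0.40 = 0.16.
- Coded rate = (1 − u) × 0.15.
- True rate = (1 − u) × 0.15 + u × 0.15 × RR.

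| u | RR | Coded rate | True rate | Relative error |
|---|---|---|---|---|
| 0.04 | 1.5 | 0.96 × 0.15 = 14.4% | 14.4% + 0.9% = 15.3% | −0.9/15.3 = −5.9% |
| 0.08 | 2 | 0.92 × 0.15 = 13.8% | 13.8% + 2.4% = 16.2% | −2.4/16.2 = −14.8% |
| 0.16 | 3 | 0.84 × 0.15 = 12.6% | 12.6% + 7.2% = 19.8% | −7.2/19.8 = −36.4% |

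If the unobserved have the same risk (RR = 1), the relative error equals −u, that is −4% to −16%.

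For associations, unequal capture matters more than the overall rate. With equal true rates but capture of 95% in one group and 75% in another, the observed ratio is 0.75/0.95 = 0.79. With 95% and 85% it is 0.85/0.95 = 0.89. In two assumed groups of 250, an ordinary two-sided 5% test of proportions would then find a false difference with these probabilities:

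| True rate | Capture 95% vs 75% | Capture 95% vs 85% |
|---|---|---|
| 20% | 22% | 8% |
| 40% | 47% | 15% |
| 60% | 77% | 27% |

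The plan selects edges by the Bayesian information criterion, not by this test, so these figures show only that spurious edges are possible.

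**Direction.** Sparse records before admission can make an old condition, first coded after IETP, look like a new diagnosis. That error runs opposite to the undercount of events after discharge.

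**The case against.** A reader might infer that patients without records are counted as having no condition and no adverse outcome. The article does not say so. It prints no coding rule for absent records, and a condensed article may leave such a rule to the full protocol or analysis plan. The missing rule is therefore not the point. The point is the completeness inference, which is printed and does not follow.

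A second tempting reading is that the article treats outcomes after discharge as complete. It does not. The quoted sentence belongs to the phenotype analysis and speaks partly of treatment provided, whereas Power and Missing Data expects most missingness after discharge. This stands. But expecting missingness does not settle when an unrecorded diagnosis or event counts as missing, and the planned rule depends on that.

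Third, the gap before admission is probably limited. Most participants are on active duty at treatment and DoD data are linked. TBI history and symptom inventories at admission also enter the phenotypes, and baseline status is abstracted from charts. This stands too: it cannot be claimed that people with few visits will fall into a low-comorbidity phenotype. Likewise, the limit in the Measures section is on VHA data, not on the combined linkage.

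Finally, the illustration takes the unobserved as worse off, and its upper end stacks three extreme assumptions. Nothing in the article supports that direction, so the claim that people with the worst course would appear as successes goes beyond the evidence.

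**Conclusion.** The concern holds in conditional form. The article infers person-level completeness from visit-level coding. The inference fails for people with no visits or with care outside VA and DoD, chiefly after they leave service. Because linked data supply phenotype inputs and health-system outcomes, and the missing-data rule sees only values marked as missing, such people may be misread as condition-free or event-free.

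The size cannot be derived from the document. The range of about 6% to 36% understatement illustrates what assumed separation, non-use and risk figures would give if absent records were read as none. It is not an estimate. Bias in the associations could run in either direction. The analysis is declared exploratory, but it is meant to inform which components are kept or dropped, so the premise is worth correcting.

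**What to change.** 1. Delete the inference from visit-level coding to little or no missing data.
2. From the linked files, derive each person's DoD or VA coverage in one fixed window before admission and one fixed window after discharge.
3. When a window is not covered, set the linked diagnoses, use and adverse outcomes for it to missing rather than none. Post-discharge values then count toward the 10% trigger in Power and Missing Data and enter structural EM. That trigger is worded for follow-up measures, so uncovered pre-admission values should be treated as missing in the mixture model itself.
4. Tabulate coverage by site and phenotype.

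The cost is extra derivation from files that are already to be linked, and slightly fewer usable linked outcomes. Two limits remain. Structural EM corrects only for missingness explained by observed factors, so it would not remove bias if people leave coverage for unrecorded reasons related to outcome. And a covered person with no visits still reads as none recorded, which is right for use but for diagnoses should be described as not recorded rather than absent.
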